### Ethical considerations

Ethical approval was obtained from the Universiti Sultan Zainal Abidin Human Research Ethics Committee, Malaysia, on August 24, 2020, with reference No. UniSZA/UHREC/2020/184. The ethics committees approved the consent form, information letter, and study consent procedure. The study protocol was registered with ClinicalTrials.gov on January 15, 2021 (Identifier No: NCT04711525). Any amendments to the study protocol will be submitted for ethical approval prior to implementation. Written informed consent will be obtained from all parents/caregivers prior to the commencement of the study. Verbal assent will be sought from children prior to their enrolment in the study [47]. The participants will be informed and shall receive an explanation regarding the purpose of the study. The participants are given the right to refuse or not to participate in the study. They will then be given the consent form during the baseline visit. After signing the form, a copy of the signed consent form will be returned to the respective participants and kept for their records. No financial compensation will be provided for all participants.

Adverse events will be monitored, reported, and handled appropriately. Existing studies on the weight-related behavioural intervention of child-parent dyads provide no evidence of any associated risks, deterioration, or complications. Even though the possible adverse events directly related to the intervention are low, all adverse events reported spontaneously by the participant or observed by the researcher or mindfulness preschool teachers will be documented and reported to the relevant research review boards within 24 hours. Adverse events include emotional distress caused by a trial procedure (either the outcome assessments or the intervention delivery). Participants are entitled to withdraw from the study at any point and do so with no disadvantage. Participation in the study may be discontinued at all times with no obligation to provide a reason.

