#### Child-parent dyads recruitment

A list of children attending the included preschools will be obtained from the preschool teachers. All child-parent dyads in the preschools will be screened for eligibility criteria, and then consent to participate will be obtained from them. Teachers will distribute the information sheets and consent forms to preschool children to deliver to their parents. Information sheets and consent forms will have an explanation of the nature of the research, study components, and the requirements of the participants. Once consent forms are collected and eligible child-parent dyads are determined, the baseline data will be collected. After completing the baseline measurements, the child-parent dyads will finally be enrolled in the intervention programme. (see Fig 1 for study outline).

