### Blinding

The single-blind RCT will be applied in the present study, in which the researcher but not the study participants know which intervention will be allocated at the preschool level. On the other hand, participants do not know to which group they will be assigned to improve external validity [39]. The single-blind method minimises bias and ensures that subjects’ knowledge of intervention assignments may not influence their response to the intervention programme [37].

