### Data collection

#### Outcomes

The primary outcome measure is the BMI z-score. The secondary outcomes measures are children’s dietary intake, physical activity, screen time duration, health-related quality of life, parental self-efficacy, parental role modelling, and parental policies. All the outcomes will be assessed at baseline, immediately following the intervention completion (3 months’ post-baseline), and at 6 months’ follow-up (9 months’ post-baseline) using anthropometric measurements (weight and height), three-day food record, and validated questionnaires. The participant’s timeline is presented in Table 2.

**Table 2 pone.0276843.t002:** Schedule of enrolment, interventions, and assessments in the *i-MaCHeL* programme. SPIRIT table as recommended by the 2013 SPIRIT Statement.

Activity & assessment	Study period								
	Enrolment	Allocation	Baseline	3-month intervention period			3-month post-baseline	6-month follow-up	Close-out
Timepoint	Oct 21—Mar 22	Apr 22	Month 0	Month 1	Month 2	Month 3	Month 3	Month 9	Jan 23

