**Enrolment**									
Contact schools	x								
Eligibility screen	x								
Informed consent	x								
Allocation		x							

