### Data management

The data generated in this study are quantitative data gathered through self-administered paper-based and web-based surveys, auto-generated website usage data, and anthropometric measures. In ensuring generated data are reliable, valid, and usable, the study used validated questionnaire items and standard procedures for the anthropometric data collection. Data collection, data cleaning, and statistical analyses will be performed by members of the research team. Study staff involved in data collection and management will be trained in implementing the procedures before and during data collection or management activities.

Once eligible child-parent dyads are determined, the children’s anthropometric data (BMI) and parent data will be collected within two weeks. Teachers will distribute the sealed envelopes to preschool children to deliver to their parents. The envelopes contain a set of three-day food record booklets and a child’s physical activity questionnaires. Parents will be asked to complete the questionnaires with their children throughout the study. After completing the surveys, the parents will return the completed food record booklet and questionnaires to preschools in sealed envelopes. The surveys will be kept by head teachers and subsequently collected by researchers. The researcher will check all completed forms for completeness and accuracy. When necessary, missing information will be requested and added during the parent’s visit to the preschool or by phone call. For the web-based surveys, the force step completion function will be used to prevent missing data, so informants can only continue with the questionnaire when all items are completed [62].

Data quality and maintenance of confidentiality will be regularly monitored by the supervisors. Outcomes of this data monitoring will be summarised in an overview and reported to all research personnel. During monthly study staff meetings, outcomes of this data monitoring will be summarised in an overview and reported to all research personnel [62]. Supervisors will regularly review data collection and management procedures at study staff meetings throughout the intervention period to ensure that they follow with fidelity and address any issues or barriers to implementation.

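### The order of consent, baseline and allocation is inconsistent, and by Table 2 the baseline measurements follow an allocation the researcher knows

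*Protocol article*

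**What the plan says.** The protocol article touches the sequence in five places.

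- **Outcomes, Table 2** (captioned "Schedule of enrolment, interventions, and assessments in the" programme). The columns run Enrolment (Oct 21 to Mar 22), Allocation (Apr 22), Baseline (Month 0). The row "Informed consent" is marked once, under Enrolment. BMI z-score and all the other outcomes have their first mark under Baseline.
- **Child-parent dyads recruitment.** "Once consent forms are collected and eligible child-parent dyads are determined, the baseline data will be collected". The section ends: "After completing the baseline measurements, the child-parent dyads will finally be enrolled in the intervention programme". It does not mention randomisation.
- **Data management.** Once eligible dyads are determined, the children's "anthropometric data (BMI) and parent data will be collected within two weeks". Members of the research team collect the data.
- **Ethical considerations.** One sentence says: "Written informed consent will be obtained from all parents/caregivers prior to the commencement of the study". A few sentences later, about the same participants: "They will then be given the consent form during the baseline visit".
- **Blinding.** The trial is single-blind, "in which the researcher but not the study participants know which intervention will be allocated at the preschool level".

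Two further statements matter. Randomisation gives the assignment of the 12 preschools to an independent researcher but does not say when it happens relative to baseline. Statistical methods adjusts the primary analysis for clustering and for the baseline value of each outcome.

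**The concern.** In a cluster trial, randomising the preschools protects the comparison only if what happens to individuals before treatment is settled without knowledge of the arm. Two steps are exposed here.

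The first is baseline measurement. If it follows allocation, a team that knows the arm takes the weights and heights and handles the parent questionnaires. Those values then serve as covariates in the primary analysis, so an arm-related error in them passes into the adjusted treatment effect.

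The second is consent. If families are asked after their preschool has been allocated, those who agree can differ between arms. Adjustment for baseline BMI z-score would deal with the measured part of such a difference. It would not deal with unmeasured differences such as motivation, which bear on the behavioural outcomes in particular.

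The first exposure follows from the schedule as printed. The second arises only if the baseline-visit sentence in Ethical considerations is the one that is followed.

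**Working it through.** No sample size, power or significance level enters this point. The check sets the statements side by side and does the calendar arithmetic.

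**1. Consent against allocation**

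| Place | Consent is obtained | Relative to allocation |
|---|---|---|
| Table 2, consent row | Enrolment, Oct 21 to Mar 22 | before (Apr 22) |
| Child-parent dyads recruitment | before baseline data | not stated |
| Ethical considerations, earlier sentence | before the study starts | not stated, naturally read as before |
| Ethical considerations, later sentence | form given at the baseline visit | after, if Table 2's column order applies |

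The last row conflicts with each of the other three. It gives consent after allocation only when combined with Table 2's column order and when Table 2's own consent row is set aside.

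**2. Baseline against allocation**

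| Place | Baseline is measured | Relative to allocation |
|---|---|---|
| Table 2 | Month 0, the column after Allocation | after |
| Child-parent dyads recruitment | before entry to the programme | not stated |
| Data management | within two weeks of eligibility being determined | depends on that date |

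For Data management, eligibility screening in Table 2 ends in March 2022. A dyad cleared by 17 March has baseline by 31 March (17 + 14 = 31), before the allocation month. A dyad cleared on 31 March has baseline by 14 April, within it. If eligibility is settled family by family across the enrolment window, most baselines would precede April. If it is settled once at the end, baseline falls in April. The text fits either reading.

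**3. Where Month 0 can fall.** Close-out is Jan 23 and the last assessment is Month 9.

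- Baseline Mar 22 + 9 months = Dec 22: fits.
- Baseline Apr 22 + 9 months = Jan 23: just fits.
- Baseline May 22 + 9 months = Feb 23: after close-out.

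Month 0 is therefore no later than about April 2022, the allocation month itself. The statement that allocation precedes baseline rests on the order of the columns, not on separate calendar dates.

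**4. Who knows the arm at baseline.** Blinding says that the researcher knows it and participants do not. Data management gives data collection to the research team. Taking Table 2's order with these two statements, baseline is collected by a team that includes someone who knows the allocation.

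**The case against.** The strongest reply is that the schedule itself is sound on consent. Table 2 marks it before allocation, and two other statements agree, so the baseline-visit sentence may be loose drafting. This stands. A reader might infer that consent follows a known allocation as scheduled; the documents do not support that. They support only that one sentence conflicts with the rest and would have that effect if followed.

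Second, no text explicitly puts baseline before randomisation, so a reader who sees a flat contradiction between Table 2 and the recruitment section goes too far. That section puts baseline before entry to the programme, and Table 2 does too. Allocation and baseline may share a month, and the flow chart (Fig 1), not available here, may show the order. This also stands, but the one place that does order the two events puts allocation first.

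Third, families do not know their group, teachers rather than the researcher hand out the consent forms, and weight and height are taken by standard procedures in duplicate, with a third reading if they disagree. These features limit the harm. They do not remove it: the questionnaires are parent-reported and the team checks and completes them, and nothing says that teachers are unaware of the arm once it is released.

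Fourth, a reader might want a figure for the recruitment bias. Any such figure would need consent rates by arm and weight status, which the documents do not give. The 29.8% overweight or obese in the Introduction is for ages 5 to 17, not 5 to 6. An imbalance in BMI z-score at entry would also be largely absorbed by the baseline adjustment, so it cannot be read as bias against the 0.14 target difference.

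Finally, a reader might extend the point to who measures at 3 and 9 months or how arms are coded for the analyst. The article is silent on both, and such detail is commonly left to a full protocol or SAP. Neither is part of this point.

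**Conclusion.** The point holds as an inconsistency in the order of events with one direct consequence. By Table 2, baseline BMI z-score and the parent questionnaires, which the primary and secondary analyses use for adjustment, are collected after an allocation the researcher knows. Separately, the baseline-visit consent sentence contradicts the recruitment section, Table 2 and its own paragraph. If it governed, it would open the trial to recruitment bias that baseline adjustment only partly removes.

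The extent is every baseline measurement in the 12 preschools, 460 dyads as planned. The size of any bias cannot be derived from the documents. The conclusion assumes that Table 2's columns are meant as a time sequence and that Fig 1 does not set out a different one. It should be corrected because the change is cheap and closes the risk.

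**What to change.** State one order in Child-parent dyads recruitment, Data management, Ethical considerations and Table 2:

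1. Consent forms collected and eligibility settled in each preschool, and the list of dyads closed.
2. All baseline measurements and questionnaires completed in all 12 preschools.
3. Allocation released by the independent researcher already named under Randomisation.

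In Table 2, move the Allocation column after Baseline. In Ethical considerations, replace the sentence that hands out the form at the baseline visit with one that places consent before baseline and before allocation. Add to Randomisation that the assignment is withheld from the research team and the preschools until step 2 is complete. Check Fig 1 for the same order.

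The cost is rewording and a short hold on allocation until the last baseline visit. The printed calendar allows this if baseline is finished by April 2022, since Month 9 is then no later than January 2023. A hold that pushed Month 0 into May would move close-out to at least February 2023. No extra staff or measurements are needed.

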### Significance and outlook

Considering the severe consequences of paediatric obesity and the high likelihood of becoming obese in adulthood [65], there is a strong rationale for focusing, planning, and evaluating the weight-related behaviour intervention programme among preschool-aged children. The present study aims to assess the efficacy of the *i-MaCHeL* programme for preschool child-parent dyads. The *i-MaCHeL* is a theory-guided, 3-month programme developed to educate child-parent dyads in encouraging healthy lifestyle behaviour among preschool children. The *i-MaCHeL* programme will target multifactorial weight-related behaviour, which are diet, physical activity, and sedentary behaviour.

The National Plan of Action for Nutrition of Malaysia III (NPANM III) 2016–2025 is a ten years plan for addressing food and nutrition challenges in Malaysia [42]. The NPANM III has also focused on promoting healthy eating and active living for Malaysian communities. Various activities related to the school setting have been identified under the NPANM III to be implemented at the national level by the Ministry of Health Malaysia (MOH) and the Ministry of Education Malaysia (MOE) agencies. The activities such as reviewing curriculum specifically for healthy eating components, developing healthy eating educational tools, and involving parents in promoting healthy eating have been identified as effective strategies under the NPANM III. Therefore, the development of the *i-MaCHeL* programme is in line with the framework of NPANM III. *The i-MaCHeL* focuses on early childhood intervention and empowering the role of parents as gatekeepers of their child’s diet and physical activity. If found to be efficacious, the *i-MaCHeL* programme may have the potential to be a new programme for the Ministry of Education Malaysia (MOE) to assist preschool teachers in promoting a healthy lifestyle in early childhood education. Besides that, the *i-MaCHeL* programme may serve as a guideline in developing suitable recommendations and nutritional interventions for communities, which may help reduce the burden of the Ministry of Health Malaysia (MOH) to overcome the complications of obesity.

The *i-MaCHeL* programme is designed with an innovative approach to delivering a health-related behaviour change programme among child-parent dyads to prevent malnutrition risk among children. The *i-MaCHeL* programme encourages children to practice a healthy lifestyle and educates parents to shape home lifestyles for optimal child growth and development. The combinations of the two modes of delivery (classroom activities and the interactive Web-based programme) will have a strong potential to be effective strategies to sustain child-parent engagement and participation in the health-related behaviour change programme. The *i-MaCHeL* programme is unique, given its Web-based approach provides an opportunity for self-paced learning, in which parents can access the *i-MaCHeL* website anytime. Moreover, the present study will contribute to the literature on online interventions for childhood malnutrition prevention, where parents are the agent of change. The findings of this study will also enhance the understanding of how parents access, use, collaborate with others, and engage in a Web-based intervention. The essential components and features of the *i-MaCHeL* programme are believed to fill the current gaps and align with the current recommendations of the childhood malnutrition intervention studies, which may lead to a more substantial impact on reducing the double burden of malnutrition in children, especially in Malaysia.

### Dissemination plans

Communication and dissemination activities will be focused on the organisations engaged in guidelines on the management of nutrition and physical activity in children, such as the Child Nutrition Sector and Nutrition Department of the Ministry of Health Malaysia and the general public. The findings of our study will be published in appropriate peer-reviewed academic journals. The findings of the study will be presented at scientific conferences.

### Plans to give access to full protocol, participant level-data, and statistical code

There are currently no plans to allow public access to the full protocol, participant-level data set, or the statistical code. Nonetheless, this will be supported by the project management committee if the researchers want to access the data set (e.g., to perform a secondary analysis or meta-analysis).
